### Data collection

Basic information regarding participants’ age, gender, prior health status, and functional capacity and the details of the resuscitation procedure will be saved in a web-based study database. Participants will be subjected to standard monitoring in the ICU. All monitored vital parameters will be saved using data collection software (S/5 Collect version 4.0, GE Healthcare, Helsinki, Finland) and a medical-approved tablet computer (Arbor M1040, Taiwan) connected to the monitor for 48 h after ICU admission.

During the first 48 h after ICU admission, ventilation settings will be obtained directly from the ventilator and saved in the study database. The doses of any sedative and vasoactive drug infusions, ABG analysis results, and other laboratory test results for the 48 h after ICU admission will be manually entered into and saved in the study database.

Regional cerebral oxygen saturation will be measured and stored continuously for 48 h after ICU admission using a non-invasive NIRS device (Covidien INVOS™ Regional Oximetry). The treating clinicians and nursing staff will be blinded to the NIRS monitoring (Fig. 3).

**Fig. 3 Fig3:**
[figure not shown]
Picture of the near-infrared spectroscopy monitor blinded from the treating personnel

Continuous four-channel EEG monitoring is applied upon admission to the ICU and recorded for 48 h after admission. The EEG recordings are collected and analyzed offline by a neurophysiologist. These EEG recordings will be categorized into three groups according to the degree of abnormality, specifically into the mild, moderate, and severe categories proposed by Crepeau et al. [37]. The doses of sedative agents (propofol, midazolam, and opioids) will be recorded in the study database. All patients undergo targeted temperature management (TTM) treatment and will receive continuous sedation according to local protocol. The study is stratified by site and we do not anticipate significant difference in the doses of sedative agents between intervention groups. However, we will report any possible differences in the amount of sedation administered between groups. The EEG analysis will also include the deepness of anesthesia (inactivity, burst-suppression, continuous slow/fast, reactive). Epileptic bursting activity in the EEG is also measured, particularly during weaning from anesthesia. Epileptic EEG activity is defined as general, lateralized, or focal bursts of spiking characterized by changes in frequency and/or location. High- or low-frequency generalized periodic discharging (GPD) in the EEG is classified as an electrophysiological sign of encephalopathy.

Additional blood samples will be obtained upon ICU admission and at 24, 48, and 72 h after cardiac arrest. The samples will be centrifuged and frozen at – 70 °C for the later analysis of serum NSE, S100b protein, and cardiac troponin concentrations or, if this is not logistically possible, for the immediate analysis of NSE, s100b and cardiac troponin using the same laboratory assays. A neurologist blinded to the study group allocations will contact all hospital survivors or their surrogates by telephone six months after cardiac arrest to determine the patients’ functional statuses using the cerebral performance category (CPC) scale.

In addition, the patients will be subject to all standard monitoring and investigations as needed according to the local protocol of the ICU. This will include prognostic evaluation in case the patient does not recover after 36-48 h.

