### Study setting and participants

Six intensive care units (ICUs) across Finland and one center in Denmark will participate in this trial. The participating Finnish hospitals are Helsinki University Hospital (Helsinki), Päijät-Häme Central Hospital (Lahti), Tampere University Hospital (Tampere), Central Finland Central Hospital (Jyväskylä), Kuopio University Hospital (Kuopio), and North Carelia Central Hospital (Joensuu). The Danish center is Aarhus University Hospital in Aarhus, Denmark. All patients admitted to one of the participating ICUs who experience ROSC after OHCA will be screened for eligibility.

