### Randomization and intervention

Schedule of enrolment, interventions, and assessments of the COMACARE trial are presented in Fig. 1. After ICU admission, participants are randomized into one of eight arms, with each arm having a different combination of PaCO_2_, PaO_2_, and MAP targets according to the 2^3^ factorial design:Low-normal PaCO_2_ (4.5–4.7 kPa), low-normal PaO_2_ (10–15 kPa), low-normal MAP (65–75 mmHg);High-normal PaCO_2_ (5.8–6.0 kPa), low-normal PaO_2_ (10–15 kPa), low-normal MAP (65–75 mmHg);Low-normal PaCO_2_ (4.5–4.7 kPa), high-normal PaO_2_ (20–25 kPa), low-normal MAP (65–75 mmHg);High-normal PaCO_2_ (5.8–6.0 kPa), high-normal PaO_2_ (20–25 kPa), low-normal MAP (65–75 mmHg);Low-normal PaCO_2_ (4.5–4.7 kPa), low-normal PaO_2_ (10–15 kPa), high-normal MAP (80–100 mmHg);High-normal PaCO_2_ (5.8–6.0 kPa), low-normal PaO_2_ (10–15 kPa), high-normal MAP (80–100 mmHg);Low-normal PaCO_2_ (4.5–4.7 kPa), high-normal PaO_2_ (20–25 kPa), high-normal MAP (80–100 mmHg);High-normal PaCO_2_ (5.8–6 kPa), high-normal PaO_2_ (20–25 kPa), high-normal MAP (80–100 mmHg).

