**Fig. 1 Fig1:**
[figure not shown]
Schedule of enrolment, interventions, and assessments of the COMACARE trial

Study centers will have access to a web-based randomization system. A cryptographically strong random number generator with modulo bias eliminated is used to generate random numbers and an unbiased Fisher-Yates (Durstenfeld) algorithm is used to shuffle blocks. Randomization is stratified with respect to target temperature (33 °C or 36 °C).

The treating clinicians and nurses will be made aware of treatment targets using laminated signs at the patient’s bedside and on mechanical ventilators (Fig. 2).

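### The protocol names target temperature as the randomization stratifier in one section and site in another, and its expectation of balanced sedation leans on the site version

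*Protocol article*

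**What the plan says.** All references are to the Protocol article.

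- **Randomization and intervention** (text after Fig. 1) describes the web-based system. It says that "an unbiased Fisher-Yates (Durstenfeld) algorithm is used to shuffle blocks" and that "Randomization is stratified with respect to target temperature", with levels 33 °C and 36 °C. Site is not mentioned and no block size is given.
- **Data collection** (text after Fig. 3), in the paragraph on EEG, says that all patients "will receive continuous sedation according to local protocol". The next sentence reads "The study is stratified by site and we do not anticipate significant difference in the doses of sedative agents between intervention groups". Target temperature is not mentioned as a stratifier. The paragraph then adds that "we will report any possible differences in the amount of sedation administered between groups".
- **Statistical analysis** names no stratification factor. It compares 48 h NSE between the low and high groups with a Mann–Whitney test and EEG category with a Chi-square test, and it rests conclusions on univariate testing.

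**The concern.** The stratification factor is a basic fact of the design, and the article gives it twice, differently. The section that defines the allocation system names temperature. A later section names site and sets it beside the expectation that sedative doses will not differ between groups.

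The second statement does some work. Sedation is given by local protocol, so doses may vary by site. The article makes depth of anesthesia part of the EEG analysis, and EEG is a secondary outcome compared without adjustment. If arms are balanced within site, local sedation habits largely cancel in that comparison. If the system stratified by temperature alone, that protection was never built in.

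The analyst also needs to know the factor. An analysis that follows the randomization cannot be specified while the article gives two answers, and the three planned papers would have to report the design consistently.

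**Working it through.** **1. The text.** No stated figure is in dispute, so the main check is to set the statements side by side.

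| Reading | Randomization section | Data collection section |
|---|---|---|
| Temperature only | correct | wrong on site |
| Site only | wrong on temperature | correct |
| Both factors | incomplete (omits site) | incomplete (omits temperature) |
| Each site uses one temperature, temperature stratified | correct | wrong: sites are pooled within a temperature stratum, so arms are not balanced within site |

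Under every reading at least one sentence needs correcting. The article does not say that both factors were used, or that temperature is fixed by site.

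**2. What within-site balance depends on.**

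Inputs from the article: 7 sites ("Six intensive care units (ICUs) across Finland and one center in Denmark will participate in this trial"), 8 arms ("participants are randomized into one of eight arms"), and 120 patients with 60 at each level of each factor (Sample size). Assumptions, because the article gives neither: sites of equal size, 120/7 = 17.1, so 17 or 18 patients; permuted blocks of eight.

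Let D be the absolute difference between the numbers of low and high patients on one factor (for example PaCO2) at one site.

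- *Temperature only.* A site's 17 patients are close to a random draw from 60 low and 60 high. With X ~ Hypergeometric(120, 60, 17) and D = |2X − 17|, the mean of D is 3.1 and P(D ≥ 5) is about 0.30. A site of 18 also gives a mean of 3.1. Simulating the two temperature strata with blocks of eight gives the same means.
- *Site only.* 17 = 2 × 8 + 1, so two complete blocks balance exactly and D = 1. For 18 = 2 × 8 + 2, the last two patients share a level with probability 3/7, so the mean of D is 2 × 3/7 = 0.86.
- *Both factors.* In a simulation with each site's patients split at random between the two temperatures and blocks of eight within each site-by-temperature stratum, the mean of D is about 1.4 at a site of 17 and 1.1 at a site of 18. D ≥ 5 occurs in about 1% of runs at a site of 17.
- *One temperature per site.* The SD of the signed difference is √[n(N − n)/(N − 1)]. With all 120 patients pooled it is √(17 × 103/119) = 3.84. With four sites of 17 in a temperature stratum (N = 68) it is √(17 × 51/67) = 3.60. Fixing temperature by site therefore recovers almost none of the within-site balance.

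The site balance on which the sedation sentence leans is thus present if site was a stratifier, alone or with temperature, and absent if it was not.

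**The case against.** The strongest defence is that the two sentences are compatible. The randomization section does not say that temperature is the *only* factor, so both may have been used and each section mentions the one relevant to it. That is possible and workable. It would still leave the section that defines the randomization incomplete, and the article never says it.

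A reader might go further and infer that using both factors would create too many strata for eight arms to balance anything. The figures do not support that. The planned comparisons are two-level margins, 60 against 60, not eight separate cells, and under the assumptions above double stratification secures most of the within-site balance (about 1.1 to 1.4 patients against 3.1). The article also does not say that every site uses both temperatures.

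A second tempting inference is that temperature-only stratification would bias the EEG or sedation results. It would not. Allocation is random under either scheme, so a site imbalance is a chance event, and the comparisons pool seven sites whose imbalances partly offset one another.

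Two further points stand. The link between site stratification and sedation is carried by *and*, not *because*; reading it as a reason is natural, given the preceding sentence on local protocols, but it is an inference. And the article does commit to recording doses and reporting sedation differences, which partly covers the risk, although reporting a difference does not adjust the EEG test.

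Finally, handling of stratifiers in the analysis is often left to an analysis plan, which is not at hand. Its absence from the article is not the finding; the conflict between two stated design facts is.

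**Conclusion.** The inconsistency is real: the article names two different stratifiers, nothing reconciles them, and at least one statement is wrong or incomplete. If only temperature was used, a typical site would show a low/high difference of about 3 patients where site-stratified blocks would leave about 1, and the expectation of balanced sedation would have no support in the design. These sizes assume equal sites of 17 or 18 patients and blocks of eight, neither of which the article states.

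The consequence is limited. The imbalance is chance and not bias, EEG is a secondary outcome of a pilot trial, and sedation differences are to be reported. A reader might infer that the primary NSE result is compromised. The documents do not support that: the sedation argument concerns the EEG comparison, and the randomization is valid for NSE under either scheme. For NSE the point is only that the test should respect whichever factor was used. This is a correction to make before analysis, not a threat to the trial's validity.

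**What to change.** 1. Check the configuration of the web-based randomization system and state the stratifier or stratifiers actually used once, in Randomization and intervention. Make Data collection agree. With 115 of 120 patients enrolled, this reports what was implemented; it does not choose a scheme.
2. If site was not a stratifier, delete the site-based reassurance about sedation and keep the commitment to report differences.
3. Analyse by the factor or factors actually used: for example, a stratified rank test (van Elteren) for 48 h NSE in place of the plain Mann–Whitney test, and a Cochran–Mantel–Haenszel test for EEG category in place of the plain Chi-square test. The planned tests take no covariate, so this means stratified versions of them, not a term added to a model.
4. If site was not a stratifier, add site-stratified comparisons of EEG category and sedative dose as a sensitivity analysis.

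The cost is a few corrected sentences, a small amount of extra analysis, and a revision of the Statistical analysis wording that rests conclusions on univariate testing. Conduct of the trial does not change.

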### Sub-study including magnetic resonance spectroscopy

For participants treated at Meilahti University Hospital, Helsinki, a magnetic resonance spectroscopy (MRS) scan will be performed 48–120 h after cardiac arrest to determine the acid-base status of the central nervous system. This is not routine practice for cardiac arrest patients; therefore, informed consent from the patient’s next of kin will be obtained before performing the MRS. The MRS scan will be performed while the patient is intubated and the patient will be monitored by a specialist in anesthesiology and a qualified ICU nurse.

Intracellular pH will be determined using ^31^P MR spectroscopy. A 6 × 6 × 6 cm^3^ voxel will be placed mainly in the parietal lobe overlapping with vascular territories of the anterior cerebral artery (ACA), middle cerebral artery (MCA), and posterior cerebral artery (PCA), utilizing T1-weighted localization images collected in three orthogonal planes. pH will be calculated by placing the chemical shift difference (δ) of Pi and PCr resonances to Hendersson–Hasselbach formula: pH = 6.77 + log{(δ-3.29)/(5.68-δ)} [38].

T2 relaxation time of water will be determined by ^1^H MRS collecting data with six different echo times (10, 25, 40, 55, 70, 85, and 100 ms) from a 15 × 15 × 15 mm^3^ voxel placed in centrum semiovale with a STEAM localization. Increased T2 serves as a marker of increased free water (edema).

### Statistical analysis

Categorical data will be presented as counts and percentages and compared with a Chi-square test. All continuous data will be checked for normality and presented as mean and standard deviation or medians with 25th and 75th quartile points. Data with a normal distribution will be compared with Student’s t-test and data with a non-normal distribution with the Mann–Whitney U test. Hourly median MAP values will be calculated from all stored MAP values and these values will be used in the analysis. Low-normal and high-normal PaCO_2_, PaO_2_, and MAP values will be compared over time using a generalized mixed model with a compound-symmetry covariance matrix. The mixed model warrants a near-normal distribution of sample and, therefore, if this is violated, logarithmic transformation will be performed and completed with a non-parametric pair-wise comparison. The values and area under the curve will be calculated for each patient and compared between the groups. In the corresponding low-normal and high-normal PaCO_2_, PaO_2_, and MAP groups, NSE levels will be compared separately at 48 h using the Mann–Whitney test. The NSE values over time will also be compared using a generalized mixed model. Kaplan–Meier curves will be constructed separately for each of the three groups to visualize survival over time. Logistic regression will be used only in case of a significant imbalance in the baseline factors, but conclusions will be based on univariate testing. The proportional distribution of EEG abnormality (categorized as mild, moderate, or severe for each patient) between treatment groups will be compared with a Chi-square test.

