### Sample size

For the power analysis, we assumed that there is no interaction between PaCO_2_, PaO_2_, and MAP and considered each intervention independently. The primary endpoint will be the NSE value at 48 h from the arrest. Based on our previous cohort of OHCA patients, the mean NSE at 48 h is around 17 μg/L and the standard deviation is around 20 [36]. In a previous, small RCT, the use of 30% FiO_2_, compared with 100% FiO_2_, resulted in approximately 50% increase of NSE values at 48 h in the subset of patients treated with hypothermia [23]. Assuming this previous finding, a study with 39 patients in each arm would have a power of 80%, with the significance set at 0.05, to detect a 50% increase in NSE. Given the possibility of death prior to 48 h and loss of follow-up, we will include 50% more patients than the target. Therefore, a total of 120 patients will be included (60 patients in each intervention arm).

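### The primary 48 h NSE comparison is unadjusted and conclusions are tied to univariate tests, so admission NSE, the randomisation stratum and the other two factors go unused

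*Protocol article*

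**What the plan says.** The primary outcome is a continuous marker; under Sample size: "The primary endpoint will be the NSE value at 48 h from the arrest". The Statistical analysis section sets the test for each of the three factors: "NSE levels will be compared separately at 48 h using the Mann–Whitney test". No covariates are named. The only rule on adjustment is: "Logistic regression will be used only in case of a significant imbalance in the baseline factors, but conclusions will be based on univariate testing".

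Elsewhere the article describes information that bears on this comparison:

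- Data collection: "Additional blood samples will be obtained upon ICU admission and at 24, 48, and 72 h after cardiac arrest". These samples are kept "for the later analysis of serum NSE, S100b protein, and cardiac troponin concentrations", so an admission NSE value is planned.
- Randomization and intervention: "Randomization is stratified with respect to target temperature", with levels 33 °C and 36 °C.
- Data collection, in the EEG text, names a different stratifier: "The study is stratified by site and we do not anticipate significant difference in the doses of sedative agents between intervention groups".
- The 2×2×2 factorial design randomises every patient to a PaCO2, a PaO2 and a MAP level.

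A mixed model of NSE over time is also planned; its covariates are not described.

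**The concern.** The primary comparison of each factor looks only at the 48 h value and that factor's two levels. Three kinds of information known at or before the start of treatment are left out: the patient's admission NSE, the stratum used in randomisation, and the levels of the other two factors. If admission NSE predicts 48 h NSE, leaving it out makes the comparison less precise than the same patients would allow.

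The adjustment rule does not repair this. A significance test of baseline balance in a randomised trial tests only chance. If it does prompt a regression, the plan says in advance that the conclusion stays with the unadjusted test. In the one situation where adjustment matters most for interpretation, it is barred from informing the result.

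At stake are the precision of the primary result and its credibility if the groups happen to differ at admission. An unseen analysis plan might well add adjusted analyses, but the article has already fixed which analysis decides.

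**Working it through.** **Inputs from Sample size.** Mean NSE 17 μg/L, SD 20, a 50% increase to be detected, significance 0.05 (taken as two-sided), 39 evaluable per arm, 60 per level randomised.

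**The plan's own figure first.** On the raw scale the difference is 0.5 × 17 = 8.5 μg/L, and n per arm = 2 × (1.96 + 0.84)² × 20² / 8.5² ≈ 87, not 39. On the log scale (below) the same formula gives 83. The 39 therefore does not reproduce. That is a separate matter; it is used here only as the article's planned evaluable number.

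**Log-scale conversion.** For a log-normal variable with mean 17 and SD 20:

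- log SD = √ln(1 + (20/17)²) = 0.932
- effect for a ratio of 1.5 = ln 1.5 = 0.405
- standardised effect d = 0.405 / 0.932 = 0.435

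**Effect of adjustment.** With correlation r between admission and 48 h log NSE, the residual SD shrinks by √(1 − r²). The standardised effect becomes 0.435 / √(1 − r²), and the gain in sample-size terms is 1/(1 − r²). The article does not give r, so a range is assumed. Power is for a two-sided t-test at 0.05.

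| Assumed r | 1/(1 − r²) | Power, 39 per level | Power, 60 per level |
|---|---|---|---|
| 0 (unadjusted) | 1.00 | 47% | 66% |
| 0.1 | 1.01 | 48% | 66% |
| 0.2 | 1.04 | 49% | 67% |
| 0.3 | 1.10 | 51% | 70% |
| 0.5 | 1.33 | 59% | 78% |
| 0.6 | 1.56 | 66% | 84% |

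The 60-per-level column treats every randomised patient as evaluable. The article expects deaths and losses before 48 h, so the 39 column is closer to its own planning.

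**Check by simulation** (4,000 runs per setting, log-normal NSE, Mann–Whitney against a linear model of log NSE with the admission value). At 39 per level, the Mann–Whitney test had about 45% power, against 50% for the model at r = 0.3 and 59% at r = 0.5. At 60 per level it had about 64%, against 69% and 77%. With no treatment effect (39 per level, r = 0.5) the Mann–Whitney test rejected in 4.4% of runs, so its overall type I error is sound.

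**Chance imbalance.** Simulating null trials with 39 per level and keeping only those with a significant difference in admission NSE, the unadjusted test's false-positive rate was about 10% at r = 0.3 and 19% at r = 0.5. These are conditional rates in the unlucky trials. They are the trials in which the plan would still conclude from the unadjusted test.

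No gain has been calculated for the temperature stratum or for the other two factors, because the article gives nothing from which to size it.

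**The case against.** The strongest reply is that the Mann–Whitney test is prespecified, suits a skewed marker and holds its type I error, so only efficiency is lost, and the size of that loss rests on a correlation that the article does not supply. This stands. The article gives prognostic value to NSE at 24–72 h and says that injury develops over the first 48 h, so a weak link with the admission value is plausible. At r = 0.1 to 0.2 the gain is only about 0 to 2 power points.

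Four stronger readings are tempting and are not supported:

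- *That logistic regression is the model for NSE.* The article never assigns it to NSE. Vital status, or a dichotomised cerebral performance category, would be natural uses. No dichotomising of NSE is planned either, so the information lost by a median split is not a cost of this plan.
- *That the imbalance trigger distorts the primary result.* With an assumed 10 independent baseline factors tested at 0.05, it would fire by chance in 1 − 0.95¹⁰ = 40% of trials. Since conclusions stay univariate, its firing cannot change them.
- *That admission NSE is thrown away altogether.* The mixed model over time may use it; the article does not say.
- *That no ratio could be produced.* The article allows log transformation for its mixed models, and a log-scale effect back-transforms to a ratio.

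What the reply does not answer is that the article itself fixes the unadjusted comparison as the basis for conclusions.

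**Conclusion.** The point holds as one of precision and robustness, not of validity. The deciding analysis of 48 h NSE is unadjusted by rule and leaves out information already planned for collection. The benefit of using it ranges from negligible (1% more patients at r = 0.1) to substantial (56% at r = 0.6). At 39 evaluable per level, power moves from 47% to between 48% and 66%. These figures assume log-normal NSE with the article's mean and SD, a true ratio of 1.5, a two-sided 0.05 test, and admission NSE available for the patients analysed. The correlation is an assumption throughout. The change is worth making because it needs no extra patients or samples and costs almost nothing if the correlation proves low.

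**What to change.** Before the outcome data are analysed:

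1. Reconcile the two statements on stratification (target temperature under Randomization and intervention, site under Data collection) and state which factor or factors were used.
2. Make the primary analysis one linear model of log NSE at 48 h on PaCO2 level, PaO2 level, MAP level, log admission NSE and the confirmed stratification factor(s). Report a ratio of geometric means with a 95% confidence interval for each randomised factor.
3. Keep the Mann–Whitney test for each factor as a supportive analysis.
4. Delete the adjustment triggered by significant imbalance and the clause tying conclusions to univariate tests. State that logistic regression applies to binary outcomes only.

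The cost is a change of wording in the analysis plan; the samples are already scheduled. The downside is reliance on a linear model on the log scale, which can be checked against the Mann–Whitney result.

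### The three ordered EEG grades are compared with a chi-square test that ignores their order, at a moderate cost in power

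*Protocol article*

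**What the plan says.** The Data collection section says that EEG recordings are "categorized into three groups according to the degree of abnormality", namely mild, moderate and severe. The scale is therefore ordered by the protocol's own definition.

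The Statistical analysis section then names the test for this outcome ("categorized as mild, moderate, or severe for each patient) between treatment groups will be compared with a Chi-square test"). This agrees with its general rule: "Categorical data will be presented as counts and percentages and compared with a Chi-square test". It gives no rank, trend or proportional-odds analysis for the EEG grade. A rank test is in the plan, but only for continuous outcomes: "data with a non-normal distribution with the Mann–Whitney U test". The same section says that conclusions will rest on univariate testing.

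CPC at six months is listed under Secondary outcomes, and Data collection describes how it is obtained. The Statistical analysis section does not name it, and the article states neither a number of levels nor a cut-point.

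**The concern.** A Pearson chi-square test gives the same p-value whichever way the three grades are labelled. It spreads its power over two degrees of freedom, covering patterns that have no clinical direction as well as a shift towards milder or more severe EEG. The Background expects a direction: it suggests that high-normal targets might go with lower brain injury markers and better neurological outcome. A graded shift is thus the natural alternative. In a pilot of 120 patients whose conclusions rest on unadjusted tests, an order-blind test lowers the chance of detecting such a shift. It also yields no effect estimate that could be carried forward.

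**Working it through.** **Plan's own figure.** The article states no power or sample size for the EEG grade, so there is none to reproduce. Its one power calculation concerns neuron-specific enolase ("a study with 39 patients in each arm would have a power of 80%, with the significance set at 0.05"), and only the 0.05 level is used here, taken as two-sided. (That calculation raises a separate question that does not bear on this point.)

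**Inputs from the article.** Three ordered grades; 120 patients, hence 60 against 60 for each factor; significance level 0.05.

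**Assumptions.** The article gives no category shares and no EEG effect. Four sets of reference shares (mild/moderate/severe) were tried, with common odds ratios (OR) of 2, 2.5 and 3 and complete EEG data.

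**Step 1: the shifted distribution.** Multiply each cumulative odds by the OR. With equal thirds and OR 2, the cumulative odds 0.5 and 2 become 1 and 4. The cumulative shares become 0.5 and 0.8, and the shifted shares are 0.50/0.30/0.20.

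**Step 2: chi-square, 2 df.** Non-centrality = n Σ(p−q)²/(p+q) = 60 × (0.0333 + 0.0018 + 0.0333) = 4.11. Power is about 42.5%.

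**Step 3: rank test, 1 df.** Non-centrality = (ln OR)² × V, where V = n₁n₂N/[3(N+1)²] × (1 − Σp̄³) and p̄ is the mean share of each grade over the two groups. Here V = (60 × 60 × 120)/(3 × 121²) × 0.877 = 8.63, and 0.4805 × 8.63 = 4.14. Power is about 53%.

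The two non-centralities are almost equal. The loss comes from the extra degree of freedom.

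**Step 4: simulation.** Multinomial sampling, 60 per group, Pearson chi-square against tie-corrected Mann–Whitney (4,000 runs per scenario; 5,000 for 40/30/30):

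| Reference shares (%) | OR 2 | OR 2.5 | OR 3 |
|---|---|---|---|
| 33/33/33 | 44.5 v 53.7 | 65.3 v 75.8 | 82.2 v 89.3 |
| 50/30/20 | 38.3 v 47.8 | 61.0 v 71.5 | 75.3 v 83.5 |
| 20/30/50 | 42.9 v 52.8 | 67.8 v 77.3 | 82.9 v 89.4 |
| 40/30/30 | 43.4 v 53.6 | 65.8 v 76.0 | 82.3 v 89.0 |

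Each cell is power in percent, chi-square v rank test. The gap runs from about 7 to 11 points. Representative values are 42% v 52% at OR 2 and 64–67% v 74–77% at OR 2.5; the 50/30/20 shares lie lower. At 39 per group (first three share sets) the gap is about 8 to 11 points. With no effect, both tests reject in about 5% of runs.

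**Step 5: in patients.** For 80% power the non-centrality must be 9.63 with 2 df and 7.85 with 1 df. The ratio is 9.63/7.85 = 1.23. If both tests have about the same non-centrality per patient, the chi-square test needs about 23% more patients.

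**Step 6: a pattern that favours chi-square.** With 33/33/33 against 20/60/20, where the middle grade swells and both extremes shrink, chi-square has about 76% power and the rank test about 5%.

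**The case against.** The best defence is that the chi-square test is valid, needs no assumption about the shape of the effect, and is applied to one secondary outcome of a pilot. Its type I error is near 5%. The power comparison was made under proportional odds, which favours the ordinal test, and step 6 shows the ranking reversing for a non-monotone difference. At OR 2 neither test is strong. All of this stands. It limits the point to a moderate gain in efficiency and means that the change has some cost. It does not remove the point, because the alternative of interest is a directional shift and a retained counts table would still show an odd pattern.

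A reader might also infer more than the article supports:

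- **That CPC is tested by chi-square on all its levels.** The Statistical analysis section never mentions CPC. Only the general rule for categorical data could reach it. If CPC is split in two, there is no order left to ignore. The full protocol or analysis plan may settle this.
- **That the plan cannot show which group did better.** Categorical data are to be presented as counts and percentages, so direction will be visible in the table. What lacks direction is the p-value.
- **That a larger trial would rely on the EEG grade.** The Discussion names survival and neurological recovery at six months for that trial.
- **That this is the epileptic-activity outcome.** Data collection defines epileptic EEG activity separately from the severity grade.

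**Conclusion.** The concern holds for the EEG grade. The article defines an ordered scale and then names an order-blind test for it. For a consistent shift with 60 patients per level, the loss is about 7 to 11 percentage points of power. This figure rests on assumed category shares, odds ratios of 2 to 3, proportional odds and complete EEG data, since the article gives none of these inputs. The planned test would not give false conclusions. It is a cheap improvement to a secondary analysis.

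No finding is made on CPC, because the form in which it is analysed is not stated.

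**What to change.** In the Statistical analysis section, replace the chi-square test as the main EEG-grade comparison. For each of the three factors (PaCO₂, PaO₂, MAP), use a Mann–Whitney or trend test or a proportional-odds model. Report the common odds ratio with its 95% confidence interval from the model, and keep the table of counts and percentages by grade. Chi-square may stay as a supporting test.

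Also state the form in which CPC is analysed. If more than two levels are compared, use the same ordinal approach; if it is dichotomised, no change is needed on this ground.

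The cost is a sentence or two and no new data; the choice should be fixed before group comparisons are seen. The drawbacks are low power against a non-monotone difference and, for the model, reliance on proportional odds.
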